### 2.3. Outcomes:

Primary outcomes:

1. Prevalence of malaria infection in children 0.5-10 years
2. Mean haemoglobin (g/dL) in children under 5 years.

Secondary outcomes:

1. Incidence of confirmed malaria episodes in children and adults through passive case detection at district health facilities
2. Sero-conversion rates
3. Entomological Inoculation Rate (EIR) for each mosquito vector species.
4. Relative population density for each mosquito vector species
5. Usage and perception of existing LLIN in baseline year
6. Evaluation of the Universal Coverage Campaign of LLIN
7. Perception and acceptance of IRS in baseline year
8. Usage and perception of LLIN in an environment of reduced IRS.
9. Detection and monitoring of resistance markers including *kdr*

Previously, in the absence of hard epidemiological data, we were unable to decide whether prevalence or incidence should be selected as our primary indicator. We think that an incidence indicator may be feasible provided we can enlist the commitment district health authorities and health centre staff to the new concept. The new concept is outlined in section 2.7. Parasite prevalence remains the primary indicator but until we have an indication of baseline prevalence we cannot estimate the number of clusters that need to be enrolled to demonstrate equivalence. Based on recent calculations it seems likely that around 30 clusters (15 clusters per study arm) will be required. One of our first activities will be to estimate prevalence in around 50 clusters in the study area. This will allow a more accurate estimation of the required sample size. We will then enrol the required number of clusters into the primary study, selecting those with the highest prevalence.

## 2.4. Hypothesis

This trial will address the following question: In a situation where IRS is thought to have been successfully deployed to reduce malaria transmission, can high coverage LLINs be implemented as a non-inferior alternative to continued IRS plus high coverage LLINs and achieve the same level of malaria control. In terms of study design the trial will, after a baseline year of IRS and high coverage of LLIN in both arms, compare high LLIN coverage along with continued use of IRS in one arm to high LLIN coverage alone in the other.

In year one (baseline) the two study arms both receive one round of high coverage IRS in January-February 2011 and Universal Coverage of LLIN at the end of March 2011. Coverage of both will be assessed. In year two (intervention year) the reference (control) study arm A continues with one round of high coverage IRS in September 2011 and high coverage of LLIN (from the distribution in March), whilst in the intervention arm (B) there will be continued high coverage of LLINs and IRS is withdrawn. The intervention arm should be no less effective than the reference arm.

## 2.5. Data analysis

Since compliance with LLIN or LLIN plus IRS allocation may not be fully adhered to, both intention to treat and per protocol analysis will be performed. To do this, household ownership and usage of LLINs and whether the house was sprayed will be determined for each individual whose infection status is measured, in each survey. Data analysis will be based on methods that make allowance for between-cluster variation (intra-cluster correlation) of responses. Data analysis will be carried out using both cluster level approaches and individual level regression approaches using random effects models. Point estimates and confidence intervals of rate ratios of malaria episodes (odds ratios of infection prevalence and anaemia) in intervention arms, relative to the reference arm, will in the first instance be based on cluster summaries. Poisson regression will be used to estimate intervention effects on malaria incidence rates and logistic regression models will be used to estimate intervention effects on prevalence of infection and prevalence of anaemia, adjusted for individual and cluster specific confounders, using random effects models.

By including vector species (*Anopheles gambiae* s.s., *An.arabiensis* and *An.funestus*) as a cluster level co-variate, it may be possible to investigate the effect of vector species on vector control effectiveness.

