#### Selecting the clusters for baseline and post interventions surveys

The selection of the determined number of clusters for the main study will be based on the following criteria determined from the pilot cross-sectional survey:

1. Clusters with the highest estimated malaria prevalence will be included.
2. Exclusion of all clusters that include any areas that have not been sprayed in the last spray round.

Allocation to the two arms will be at random, stratified by malaria prevalence and population size as determined by the pilot study.

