#### Objectives of the baseline survey

1. To determine if the two arms are similar in terms of malaria indicators
2. To determine the coverage of LLINs and evaluate the universal coverage campaign
3. To evaluate the usage and perception of existing LLIN in baseline year
4. To evaluate perception of IRS in baseline year
5. To determine the risk factors for malaria
6. To determine the effect of LLIN integrity on malaria prevalence

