### **3.8. Data collection and analysis**

Household questionnaires for the baseline and interventions cross sectional surveys will be programmed into PDAs and downloaded into Microsoft Access via Pendragon forms 5.1 software. This allows continual checking of the data without the need to wait for data entry. Entomological data will also be entered using PDAs. Clinical data will be recorded on paper in the field because these forms must be passed between the nurses doing the examination and the dispensing officer (clinician), who must approve each copy. The forms will then be double entered, validated and verified by data entry clerks in the PAMVERC office.

The full analytical plan will be developed later. Given the nature of the interventions it is not possible to conduct a blinded trial. Stratified randomisation of villages to the study groups will reduce the likelihood of chance imbalances between study arms but as only relatively small number of units can be randomized in such a cluster design, the 2 groups cannot be assumed similar for all factors. Data on parasite prevalence and anaemia will be collected for sampled children during baseline to adjust for any imbalances in malaria at clusters level. Only houses in the core sampling areas, situated at least 1 km apart from the next cluster will be selected to reduce any spill-over effect (where an anti-vector intervention may also reduce or increase transmission in neighbouring villages).

Individual data will be collected on potential confounding factors to allow for adjustments in the final analysis. Potential confounders to be probed during cross sectional surveys include home treatment/prophylaxis of malaria, travel to other areas with different levels of transmission, and the use of other anti-mosquito measures which may prevent malaria transmission such as insecticidal sprays, coils, repellents, smoke, quality of LLINs by recording the number of holes and usage and quality of spraying (using pyrethroids detection kits). Household and personal data will be analysed with parasite prevalence data to identify and quantify individual, household and environmental risk factors.

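### The first-instance cluster-summary estimate is not tied to the randomisation strata or baseline cluster prevalence, and baseline adjustment is justified only by imbalance

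*Protocol*

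**What the plan says.** Four places in the Protocol bear on this.

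- **Allocation** (section 3.3.2, on selecting the clusters): "Allocation to the two arms will be at random, stratified by malaria prevalence and population size as determined by the pilot study".
- **Analysis** (section 2.5): two approaches are planned. "Data analysis will be carried out using both cluster level approaches and individual level regression approaches using random effects models". Effect estimates and intervals "will in the first instance be based on cluster summaries". Adjustment is mentioned only in the sentence after that, for the regression models, which are "adjusted for individual and cluster specific confounders, using random effects models".
- **Purpose of the baseline data** (section 3.8): "Data on parasite prevalence and anaemia will be collected for sampled children during baseline to adjust for any imbalances in malaria at clusters level". The same paragraph says: "The full analytical plan will be developed later".
- **Baseline survey objectives** (section 3.3.3): the first one listed is "To determine if the two arms are similar in terms of malaria indicators".

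The stratification factors do not reappear in either analysis section.

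**The concern.** Stratified allocation makes the arms alike on the stratifying factors. If the analysis then ignores the strata, the variation between strata stays in the error term and the interval is wider than the design warrants. In a non-inferiority trial, a wider interval lowers the chance of excluding the margin when the arms are truly equivalent.

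Baseline cluster prevalence is a measurement of the primary outcome in the same clusters, taken before the intervention. It reduces residual variance whether or not the arms differ at baseline. Treating it as a remedy for imbalance is therefore a weak rationale, and it invites the decision to adjust to be taken after the arms have been compared. With about 30 clusters, that decision can move both the estimate and its interval.

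**Working it through.** **Inputs from the Protocol.** Section 2.3 expects about 15 clusters per arm. Section 2.6 sets m = 100 persons per cluster, 80% power and 5% significance, with sidedness not stated. Only one non-inferiority entry in Table 1 equals 15: prevalence p = 4%, margin d = 3 points, between-cluster coefficient of variation k = 0.6.

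**Assumed here, not in the Protocol.** The correlation r between a cluster's true prevalence at baseline and at follow-up is taken as 0.5, 0.7 or 0.9. Baseline and follow-up are given the same mean and spread.

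**Step 1: reproduce the plan's figure.** With equal prevalence in the two arms:

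c = 1 + (z_α + z_β)² × 2 × [p(1−p)/m + k²p²] / d²

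- Sampling variance: 0.04 × 0.96 / 100 = 0.000384
- Between-cluster variance: (0.6 × 0.04)² = 0.000576
- Variance over two arms: 2 × 0.00096 = 0.00192
- One-sided 5%: (1.645 + 0.842)² ≈ 6.18, so c = 1 + 6.18 × 0.00192 / 0.0009 = 14.19, rounded up to 15. This agrees with Table 1.
- One-sided 2.5% would give 17.74, rounded up to 18, which does not agree.

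One-sided 5% reproduces all 14 non-inferiority entries. The formula has no term for strata or baseline.

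**Step 2: power without adjustment at 15 per arm.** Power = Φ(√(14 × 0.0009 / 0.00192) − z_α), where the root is √6.5625 = 2.562.

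- One-sided 5%: Φ(2.562 − 1.645) = 82.0%
- One-sided 2.5%: Φ(2.562 − 1.960) = 72.6%

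**Step 3: effect of baseline adjustment.** The reliability of a cluster prevalence from 100 children is 0.000576 / 0.00096 = 0.60. The observed correlation is then 0.60r, and the residual variance is multiplied by 1 − (0.60r)².

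| Assumed r | Observed correlation | Variance factor | Equivalent clusters per arm (15 / factor) | Power, one-sided 5% | Power, one-sided 2.5% |
|---|---|---|---|---|---|
| none | – | 1 | 15 | 82.0% | 72.6% |
| 0.5 | 0.30 | 0.910 | 16.5 | 85.1% | 76.6% |
| 0.7 | 0.42 | 0.824 | 18.2 | 88.1% | 80.6% |
| 0.9 | 0.54 | 0.708 | 21.2 | 91.9% | 86.1% |

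**Step 4: a less favourable row.** At 4%, 3 points and k = 0.3, the between-cluster variance is (0.3 × 0.04)² = 0.000144, so reliability is 0.000144 / 0.000528 = 0.27. The variance falls by about 2%, 4% and 6%. Unadjusted power at 15 per arm is already 96.5% at one-sided 5%, and adjustment takes it to 96.7%, 97.0% and 97.2%.

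**Step 5: degrees of freedom.** Two arms of 15 leave 28. The baseline covariate uses one. Four strata, a number assumed because the Protocol gives none, would use three more and leave 24. In a t-based calculation for the k = 0.6 row with r = 0.7 and one-sided 5%, power is 88.5% with 27 degrees of freedom and 88.4% with 24.

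The separate gain from the strata is not quantified, because the Protocol does not say how many there are or how much variation they explain.

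**The case against.** The case against is substantial, and most of its parts stand.

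- **The estimate is not called crude.** Section 2.5 does not say that the cluster-summary estimate is unadjusted or unstratified, and such an analysis can be either. This stands: the wording leaves the matter open.
- **Baseline adjustment is in the plan.** Section 3.8 collects baseline prevalence in order to adjust, and section 2.5 plans regression models with cluster-level covariates. This stands. What is missing is a link to the first-instance estimate and a commitment that does not depend on imbalance.
- **No stated gate.** A reader might infer a rule that adjustment is dropped if the arms look similar. The documents do not support that: arm similarity is a descriptive objective of the baseline survey, and nothing ties it to the model. The wording permits such a choice but does not prescribe it.
- **No lost power.** A reader might also infer that adjustment is needed to restore the planned power. It is not. The 15-per-arm entry reproduces at one-sided 5% with 82.0% power and no adjustment. A shortfall (72.6%) appears only at one-sided 2.5%, a level the Protocol does not state.
- **Direction of harm.** A wider interval does not favour a false claim of non-inferiority. This stands: the loss is one of efficiency and of pre-specification.
- **Deferral.** Section 3.8 leaves the full analysis plan for later, and model details are ordinary content of such a plan. This stands only in part. The Protocol already fixes the order of the analyses and an imbalance-based reason for adjusting, and a later plan could follow both faithfully and still have the weakness.

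**Conclusion.** The point holds as one of efficiency and pre-specification. Allocation is stratified, but the strata are not carried into any analysis text. The first-instance estimate is not linked to baseline cluster prevalence, and the only reason given for using baseline prevalence is imbalance.

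In the row that yields 15 clusters per arm, always adjusting for baseline would add about 3 to 10 percentage points of power at one-sided 5%, or about 4 to 13 points if a two-sided 95% interval is used. Both ranges rest on the assumed correlations of 0.5 to 0.9. The gain would be smaller if selecting the highest-prevalence clusters narrows their spread, and at k = 0.3 it is close to nil. The number of clusters is itself provisional, since section 2.3 re-estimates it after the pilot.

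**What to change.** In sections 2.5 and 3.8, state that the primary cluster-level analysis always includes the randomisation strata and the baseline cluster prevalence, whatever the baseline comparison shows. One form is a linear model of cluster follow-up prevalence on arm, strata and baseline prevalence. For haemoglobin, use the baseline cluster mean in the same way. Report the unadjusted cluster-summary comparison as a sensitivity analysis, and keep the comparison of arms at baseline as description only.

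Settle this before any follow-up data are seen. The cost is a change of wording and a few degrees of freedom out of about 28. No new data are needed, because the pilot and baseline surveys already supply the strata and the covariates.

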## 2.6. Sample Size Estimations

The sample size is based on the principles cluster randomised trials using the margin of difference of prevalence of infection between the IRS plus LLIN and the LLIN alone arms. As the trial is intended to show non-inferiority between the LLIN and IRS study arms, power calculations have been based on an observable margin of difference between these two study arms. The cost considerations require this margin of difference to be 50% or more. It is appreciated that a 50%

---

 Hayes RJ and Moulton LH. Cluster randomised trials. Chapman Hall/CRC. New York, 2009.

relative difference between study arms may be unacceptably large when prevalence is high. For example when prevalence is high an absolute margin of difference of 20% would not constitute meaningful equivalence, whereas 2% or 3% difference may well be considered equivalent, even if this difference constitutes a relative difference of 50% or 75% respectively, when true prevalence is only 4%. Prohibitively large numbers of clusters would be required to determine non-inferiority within a smaller margin of relative difference between study arms. The baseline malaria indicator survey will be used to estimate the current prevalence of infection in the study area.

Table 1 shows the number of clusters per study arm required in superiority and non-inferiority trials respectively, for different scenarios of relative differences in prevalence of between study arms, levels of baseline prevalence of 10%, 8% and 4% respectively, and for between cluster coefficients of variation of 0.1, 0.2 and 0.3 and one scenario of 0.6. The sample size per cluster is 100 throughout; power is set at 80% and significance at 5%. The scenarios have been chosen for absolute differences between study arms of no more than 5%, which has been assumed to be the largest margin of difference that would be meaningful in a non-inferiority study, even if it represents a relative difference of 50% (or more).

We expect that the baseline survey may show prevalence to be quite low, and have therefore included scenarios where baseline prevalence is 10% or lower, and where one might want to show non-inferiority as ruling out a LLIN alone arm inferiority of more than a few percent prevalence above the IRS plus LLIN arm.

**Table 1.** Sample size scenarios

| Prevalence of infection  , % | Relative difference/margin (absolute difference) between study arms | Between cluster coefficient of variation | Persons surveyed per cluster | Clusters per arm required in SUPERIORITY trial | Clusters per arm required in NON INFERIORITY TRIAL |
|------------------------------------------|---------------------------------------------------------------------|------------------------------------------|------------------------------|------------------------------------------------|----------------------------------------------------|
| 10                                       | 50%(5)                                                              | 0.1                                      | 100                          | 6                                              | 6                                                  |
| 10                                       | 25% (2.5)                                                           | 0.1                                      | 100                          | 23                                             | 21                                                 |
| 8                                        | 50% (4)                                                             | 0.1                                      | 100                          | 7                                              | 8                                                  |
| 8                                        | 25%(2)                                                              | 0.1                                      | 100                          | 29                                             | 26                                                 |
| 10                                       | 50%(5)                                                              | 0.2                                      | 100                          | 7                                              | 8                                                  |
| 10                                       | 25%(2.5)                                                            | 0.2                                      | 100                          | 29                                             | 27                                                 |
| 8                                        | 50%(4)                                                              | 0.2                                      | 100                          | 9                                              | 9                                                  |
| 8                                        | 25%(2)                                                              | 0.2                                      | 100                          | 35                                             | 32                                                 |
| 10                                       | 50%(5)                                                              | 0.3                                      | 100                          | 9                                              | 10                                                 |
| 10                                       | 25%(2.5)                                                            | 0.3                                      | 100                          | 39                                             | 37                                                 |
| 8                                        | 50%(4)                                                              | 0.3                                      | 100                          | 11                                             | 12                                                 |
| 8                                        | 25%(2)                                                              | 0.3                                      | 100                          | 45                                             | 42                                                 |
| 4                                        | 75%(3)                                                              | 0.3                                      | 100                          | 7                                              | 9                                                  |
| 4                                        | 75%(3)                                                              | 0.6                                      | 100                          | 11                                             | 15                                                 |

## 2.7. New incidence indicator

The establishing of incidence through passive case detection in the existing primary health care (PHC) system is feasible and has the advantage of building upon the existing health care structures. The current PHC system based on government and private (e.g. missionary) funded health facilities is staffed by committed and experienced health care workers. Such facilities are in place throughout the district and their exact locations have recently been mapped by project staff (Fig 3). What is currently lacking is the means to accurately diagnose malaria and to manage it properly. Some facilities diagnose clinically, some through microscopy, and all prefer RDTs when they are available. Because of frequent RDT stock-outs it is impossible to assess the true burden of malaria or show if it is declining as a result of the PMI IRS programme. If RDTs and ACTs were to be made available throughout the year the basic means to diagnose malaria would be in place. If the registration system were then to be modified to record each patient's age and hamlet, village and ward of residence the basic system needed to determine passive case incidence and the impact of the PMI control programme would be established. Three outcome variables would emerge from such a system: 1. the number of malaria cases per year by cluster and age group, 2. the ratio of malaria to other causes of febrile illness (equivalent to the indicator 'slide positivity rate' in countries where microscopy is conventionally used) and 3. incidence rates among registered

 Prevalence in control arm for superiority study; true prevalence in non-inferiority study

families from the clusters. For the duration of the project copies of the records would need to be collected from the health centres on a monthly basis and then the data would need to be entered into an access database to allow analysis.

Establishing such a system has many benefits not just to the project but to PMI's greater aims:

1. It provides a role for the general health services and the District Medical Officer in monitoring progress of the malaria control programme.
2. It improves the quality of the PHC system to improve diagnosis and treatment of malaria.
3. If PMI were to scale down its control programme and withdraw from the area, a system would be in place to provide continued management of malaria, possibly reducing any risk of re-emergence and could provide a warning system if malaria transmission started to increase.

Establishing such a system cannot be done by the Project itself. It requires commitment, partnership and coordination between the Project, PMI, USAID, NMCP, DMO, general health service facilities. There is a clear role for PMI in making sure that adequate resources (RDTs and ACTs in particular) are made available to ensure year round diagnosis and treatment ad libitum, and to ensure that its partners (RTI and local PMI) commit to the endeavour. Coordination mechanisms need to be put in place. All partners need to be fully committed. If all goes to plan a model for provision of diagnosis and treatment will be established that can then be replicated in other areas.

The inspiration for this system arises in part from the study done by [name] and colleagues in RTI and PMI/CDC in which RDTs were supplied to 17 health facilities in IRS and non-IRS areas of Kagera, where it was shown that positivity rates fell from 9.6% to 2.8% in control and sprayed areas respectively ([name] et al. 2010). Similar approaches to monitoring incidence have been established in other countries and are feasible in Muleba.

